### Sample size

The sample size calculation is based on the primary aim of comparing biologically verified 7-day PPA between the QT group and the WQ group at the 1-month follow-up. We used the following assumptions: (1) significance level of 0.05 for a two-sided test; (2) statistical power of 90%; (3) biologically verified 7-day PPA at the 1-month follow-up in the QT group is conservatively estimated as 20% based on the data from California Smokers’ Helpline [19]; (4) an increase in abstinence rate of 15% in the WQ group compared with the QT group; (5) a dropout rate of 20%. Considering the random block size (4 or 6), 460 eligible patients (230 for each group) will be required in this study.

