### Statistical analysis plan

All statistical analyses be analyzed and blinded to the intervention assignment by a statistician using SPSS version 22.0 software (SPSS, Inc., Chicago, IL). Data will be presented as mean (standard deviations) for continuous variables with normal distribution; median (inter-quartile range) for continuous variables without normal distribution; and proportions for categorical variables. Baseline characteristics of participants in the intervention and control groups will be compared using Student’s t-test or non-parametric test for continuous variables and Pearson's chi-square or Fisher's exact test for categorical variables.

Multiple logistic regression will be used for between-group comparisons of the primary outcome variable-biochemically validated 7-day PPA at the 1-month follow-up and the secondary outcomes- self-reported 7-day PPA at the 1-, 3-, 6-, and 12-month follow-up and self-reported continuous smoking abstinence from 1-month to 12-month, with odds ratio (OR) and 95% confidence intervals (CI) to assess between-group effects. By intent-to-treat analysis (ITT), participants who are lost to follow-up or refuse to participate in the validation tests will be considered as continuing smokers with no reduction in cigarette consumption compared with baseline. Participants who do not use smoking cessation services after randomization will be excluded from the ITT analysis data set. In addition, we will conduct a per-protocol (PP) analysis of the primary outcome among the participants in the QT group who receive at least one telephone session and those in the WQ group who use the QUIT WMP for at least 20 days and send more than 10 short messages in the QUIT WG. For comparisons of secondary continuous outcomes with non-normal distribution assumptions, Mann–Whitney tests will be conducted. Subgroup analyses will assess the efficacy in participants with different demographics, baseline smoking characteristics, combined chronic diseases, and use of intervention variables (including compliance of using NRT gum, frequency and duration of using WeChat- or quitline-based cessation services) using multiple logistic regression. No interim analysis will be conducted. A two-sided *P* value of < 0.05 will be considered as statistically significant difference.

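### The dropout allowance behind 460 participants assumes dropouts leave the analysis, but the plan counts losses as smokers; the power is about 88% or about 95%, depending on what the 20% and 35% describe

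*Protocol article*

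**What the plan says.** The Sample size section of the protocol article lists these inputs for verified 7-day abstinence at 1 month:

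- a "significance level of 0.05 for a two-sided test" and 90% power;
- a rate of 20% in the quitline (QT) group;
- "an increase in abstinence rate of 15% in the WQ group compared with the QT group", which gives 35% in the WQ group if read as percentage points;
- 20% dropout.

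It concludes: "a dropout rate of 20%. Considering the random block size (4 or 6), 460 eligible patients (230 for each group) will be required".

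The Statistical analysis plan section gives the rule for the primary analysis: "participants who are lost to follow-up or refuse to participate in the validation tests will be considered as continuing smokers". The sentence after that rule takes participants who use no cessation service after randomisation out of the data set that the protocol calls intent-to-treat.

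The Sample size section does not define dropout. It also does not say whether 20% and 35% are rates among people followed up or among everyone analysed.

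**The concern.** Dividing a sample size by one minus the dropout rate protects power when dropouts disappear from both numerator and denominator and the assumed rates hold among those who remain. Here, people lost to follow-up stay in the denominator as failures. The sample then does not shrink as the inflation supposes. Instead, both abstinence rates and the gap between them shrink.

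The stated 90% is therefore tied to a different analysis from the planned primary one. Depending on what the two rates mean, the power of the planned analysis is somewhat lower or clearly higher than stated. A reader who uses the stated power to interpret the result cannot tell which.

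**Working it through.** **Inputs.** From the Sample size section: two-sided alpha 0.05 (z = 1.960), power 90% (z = 1.282), rates 0.20 and 0.35, dropout 0.20, 230 per group. The 15% increase is taken as absolute, because a relative increase (20% to 23%) would need about 3,939 per group. Assumption added here: loss is 20% in each group.

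**1. Reproduce the plan's figure.** Pooled two-proportion formula, with p̄ = 0.275:

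n = [1.960 × √(2 × 0.275 × 0.725) + 1.282 × √(0.20 × 0.80 + 0.35 × 0.65)]² / 0.15²
= (1.238 + 0.798)² / 0.0225 ≈ 184.1 per group.

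184.1 / 0.8 = 230.2, so 230 per group and 460 in total. The arcsine formula gives 184 and exactly 230. Rounding the pooled result up to 185 first gives 232 (464 in total), still within 1% of 460. The power with 184 per group is 90.0%. The stated figure therefore reproduces, and it does so with dropouts removed.

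**2. Apply the analysis rule, taking 20% and 35% as rates among those followed up.** With 20% lost and counted as smoking:

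- QT: 0.20 × 0.8 = 0.16
- WQ: 0.35 × 0.8 = 0.28
- difference: 0.12 instead of 0.15

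Power with 230 per group, p̄ = 0.22:

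- standard error under the null = √(2 × 0.22 × 0.78 / 230) = 0.03863
- standard error under the alternative = √((0.16 × 0.84 + 0.28 × 0.72) / 230) = 0.03822
- Φ[(0.12 − 1.960 × 0.03863) / 0.03822] = Φ(1.159) = **87.7%**

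Exact enumeration of the chi-square test gives 87.9%. On this reading, 90% power would take 249 per group (498 in total).

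**3. Allow for the exclusion of non-users.** Let e be the share of the 20% dropouts who used no service and are excluded. With k = 1 − 0.2e, the analysed number is 230k per group and the rates are 0.16/k and 0.28/k.

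| e | Analysed per group | Power |
|---|---|---|
| 0 | 230 | 87.7% |
| 0.5 | 207 | 88.7% |
| 1 | 184 | 90.0% |

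**4. Take 20% and 35% as rates that already count losses as smoking.** All 230 per group then contribute at 0.20 versus 0.35:

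Φ[(0.15 − 1.960 × √(0.39875 / 230)) / √(0.3875 / 230)] = Φ(1.666) = **95.2%**

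About 184 per group would have been enough for 90%, so the inflation was not needed.

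**The case against.** **The plan does remove some people, so 90% may be right.** This stands in part. A reader might infer that no reading of the protocol yields 90%. The documents do not support that: non-users of services are excluded and dropout is undefined, so 90.0% is recovered if every dropout is an excluded non-user. But then nobody would be lost after using a service, and the rule counting losses as smokers would have nothing to act on. With any loss after service use, power on the completer-rate reading falls below 90%.

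**The shortfall is too small to matter.** It is at most 2.3 points, it rests on planning assumptions, and on the other reading the plan is better powered than it says. This settles the size of the point but does not remove the mismatch between the two sections.

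**Refusal of the CO test.** A reader might infer that power falls well below 88% because refusers also count as smokers. The documents do not establish this. They give no refusal rate, and the assumed 20% is already described as a verified rate. Under the outcome definition an untested person is not confirmed abstinent, so refusers may already be inside the 20%. Applying a further reduction could count them twice. The protocol only needs to say whether they are included.

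**The word conservatively.** The text says the QT rate "is conservatively estimated as 20% based on the data from California". A reader might object that, with a fixed 15-point gap, a low control rate is the favourable assumption. That holds only on the absolute scale. The planned effect measure is the odds ratio, here (0.35/0.65)/(0.20/0.80) = 2.15. At that odds ratio with 184 per group, power is 84% at a control rate of 15% and 90% at 20%, so a low rate is then the cautious choice. The wording can stay.

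**Conclusion.** The point holds as a minor correction. The allowance for dropout in the Sample size section does not match the handling of losses in the Statistical analysis plan section.

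- If 20% and 35% are rates among those followed up, which is what the inflation implies, power with 460 participants is about 88% (87.7%). It approaches 90% only as more of the dropouts are excluded non-users.
- If the rates already count losses as smoking, power is about 95%.

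These figures assume the protocol's own rates and its 20% dropout, equal in both groups, and an unadjusted comparison of two proportions. The sample size is not shown to be inadequate, and the mismatch alone gives no reason to enlarge the trial.

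**What to change.** Keep 460 and amend the Sample size section as follows.

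1. Say whether 20% and 35% are rates among participants followed up or among all those analysed with losses counted as smoking.
2. Say whether both rates already count participants who refuse the CO test as smokers.
3. Restate the power to match the primary analysis, using one of these:
   - *Completer rates:* With 20% of participants lost in each group and counted as smokers, the analysed rates are 16% and 28%, and 230 per group give about 88% power. If part of the 20% is expected to be non-users excluded from the analysis, give that share; the power then lies between 87.7% and 90.0%.
   - *Rates with losses already counted as smoking:* 230 per group give about 95% power for 20% versus 35%, and no dropout inflation is applied.

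The cost is a change of wording. No participants are added and the analysis does not change. On the completer-rate reading, the stated power becomes slightly less favourable.

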### Data management

Data from all questionnaires and assessment scales will be collected electronically via the Tencent questionnaire platform. These data will be integrated with data on the use of smoking cessation services downloaded from the Quitline and WeChat platforms. Participants' cell phone numbers were used as unique identifiers.

All study files will be stored securely in password-protected computer files. Only the principal investigators of the study ([name] and [name]) will be given access to the cleaned full data sets. A data monitoring committee (DMC) has been established and composed of clinicians and statisticians independent of clinical trials, which will be responsible for monitoring study conduct, safety, effectiveness and adaptive design. It is independent from the sponsor and has no role in the design of this study and will not have any role during its execution, analyses, interpretation of the data, or decision to submit results.

### Statistical analysis plan

All statistical analyses be analyzed and blinded to the intervention assignment by a statistician using SPSS version 22.0 software (SPSS, Inc., Chicago, IL). Data will be presented as mean (standard deviations) for continuous variables with normal distribution; median (inter-quartile range) for continuous variables without normal distribution; and proportions for categorical variables. Baseline characteristics of participants in the intervention and control groups will be compared using Student’s t-test or non-parametric test for continuous variables and Pearson's chi-square or Fisher's exact test for categorical variables.

Multiple logistic regression will be used for between-group comparisons of the primary outcome variable-biochemically validated 7-day PPA at the 1-month follow-up and the secondary outcomes- self-reported 7-day PPA at the 1-, 3-, 6-, and 12-month follow-up and self-reported continuous smoking abstinence from 1-month to 12-month, with odds ratio (OR) and 95% confidence intervals (CI) to assess between-group effects. By intent-to-treat analysis (ITT), participants who are lost to follow-up or refuse to participate in the validation tests will be considered as continuing smokers with no reduction in cigarette consumption compared with baseline. Participants who do not use smoking cessation services after randomization will be excluded from the ITT analysis data set. In addition, we will conduct a per-protocol (PP) analysis of the primary outcome among the participants in the QT group who receive at least one telephone session and those in the WQ group who use the QUIT WMP for at least 20 days and send more than 10 short messages in the QUIT WG. For comparisons of secondary continuous outcomes with non-normal distribution assumptions, Mann–Whitney tests will be conducted. Subgroup analyses will assess the efficacy in participants with different demographics, baseline smoking characteristics, combined chronic diseases, and use of intervention variables (including compliance of using NRT gum, frequency and duration of using WeChat- or quitline-based cessation services) using multiple logistic regression. No interim analysis will be conducted. A two-sided *P* value of < 0.05 will be considered as statistically significant difference.

An economic evaluation will be conducted alongside this RCT following the approach of Drummond et al. [45] and in concordance with the Consolidated Health Economic Evaluation Reporting Standards statement [46]. The ICER will be calculated as follows: ICER = (C1 − C0) / (E1 − E0), where C refers to costs, E refers to effect, and the subscripts 1 and 0 refer to the WQ and QT groups, respectively. We will generate 2500 replicate samples by bootstrap and estimate the corresponding incremental costs and effects for each replicate sample, which are then plotted on a cost-effectiveness plane.

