#### Follow-up measures

All participants will complete 1-, 3-, 6-, and 12-month follow-up assessments over the phone or online using the Tencent Questionnaire platform at participants’ convenience. Three non-participating staff will conduct the telephone follow-ups. The follow-up assessment information includes smoking status, quitting attempts, acceptability and satisfaction of the cessation services, and the usage of smoking cessation services, etc. A scale of 0 to 10 (0: not at all; 10: very high) for acceptability and satisfaction with each service will be evaluated. Participants who report quitting smoking or reducing their consumption of cigarettes will fill out the Minnesota Nicotine Withdrawal Scale (MNWS) [40] and the Brief- Questionnaire of Smoking Urges (QSU Brief) [40]. Adverse events and other unintended effects of interventions during the intervention period will be spontaneously reported. At 1-month follow-up, individuals with self-reported smoking abstinence for more than 7 days will be invited to participate in an exhaled carbon monoxide (CO) test for biochemical validation. To increase follow-up compliance, participants will receive 100 RMB (approximately US $ 14.95) in the form of the WeChat red packet (Hongbao, which is similar to an electronic cash reward [41]). The full list of measurements is presented in Table 3.

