#### Outcomes

The primary outcome is biochemically validated 7-day point prevalence of abstinence (PPA) at the 1-month follow-up [42], defined as the proportion of smokers who self-report not even a puff of smoke in the past 7 days at the 1-month follow-up and are confirmed by a carbon monoxide level in expired air of less than 3 parts per million (ppm) [43].

Secondary outcomes include self-reported 7-day PPA [42] at the 1-, 3-, 6-, 12-month follow-up, self-reported continuous smoking abstinence rate (defined as the proportion of participants who are smoking less than 5 cigarettes [42]) from the 1-month to 12-month follow-up, self-reported quit attempts rate (defined as the proportion of participants who are continuously smoking but have tried to quit smoking for at least 24 h [44]) at the 1-, 3-, 6-, 12-month follow-up, acceptability and satisfaction scores of the services, incremental cost-effectiveness ratio (ICER) of the services.

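### The rule that scores CO-test refusers as smokers is not limited to the CO-validated outcome, so as worded it also overwrites 1-month self-reported abstinence

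*Protocol article*

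**What the plan says.** All references are to the protocol article.

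- **Outcomes.** The primary outcome is 7-day PPA at 1 month, self-reported and confirmed by expired CO below 3 ppm. The secondary list is separate: "Secondary outcomes include self-reported 7-day PPA" at 1, 3, 6 and 12 months, with no CO condition.
- **Follow-up measures.** CO testing is a further step after the self-report, at 1 month only: "individuals with self-reported smoking abstinence for more than 7 days will be invited to participate in an exhaled carbon monoxide (CO) test". Anyone who refuses it has therefore already reported abstinence.
- **Statistical analysis plan.** One sentence assigns logistic regression to the primary outcome, to self-reported PPA at all four visits and to continuous abstinence. The next gives the intention-to-treat rule: "participants who are lost to follow-up or refuse to participate in the validation tests will be considered as continuing smokers". It adds that their cigarette consumption is taken as unchanged from baseline. No outcome or visit is named.

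**The concern.** There are two linked problems.

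The first is in the text. The rule joins two groups that need different treatment. People lost to follow-up have no self-report. CO refusers have one, and it says abstinent. Because the rule is unrestricted, it replaces that answer with its opposite in an outcome defined by the answer.

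The second is what this takes away. Scoring refusers as non-abstinent is not neutral for the primary comparison if abstainers refuse more often in one arm. The trial is open label and the arms have different contact: app and group activity with daily reminders in WQ, scheduled telephone sessions in QT. Different CO-test uptake is therefore possible. The natural comparison is 1-month self-reported PPA: a gap in the validated outcome without one in the self-report would suggest differing uptake (or differing CO failure) rather than differing abstinence. If the rule overwrites the self-report, that comparison is lost.

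**Working it through.** **1. The text, side by side.** Take a participant who completes the 1-month questionnaire, reports no smoking in the past 7 days and declines CO.

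| Outcome at 1 month | By its definition (Outcomes) | By the rule as worded |
|---|---|---|
| CO-validated 7-day PPA | not abstinent (unconfirmed) | smoker |
| Self-reported 7-day PPA | abstinent | smoker |

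The first row agrees; the second does not. Under the rule as worded, the self-reported outcome differs from the primary only through people who take the CO test and fail it. The clause on unchanged consumption also shows that the sentence reaches beyond the primary outcome, since consumption is not part of the primary definition.

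**2. The plan's own figure.** Inputs from Sample size: "significance level of 0.05 for a two-sided test", 90% power, 20% in QT, "an increase in abstinence rate of 15% in the WQ group compared with the QT group" (so 35%), and 20% dropout.

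- Pooled variance: n = [1.960 × √(2 × 0.275 × 0.725) + 1.2816 × √(0.2 × 0.8 + 0.35 × 0.65)]² / 0.15² = 184.1, so 185 per arm. 185 / 0.8 = 231.25, so 232 per arm, 464 in total.
- Unpooled variance: 181 per arm. 181 / 0.8 = 226.25, so 227 per arm, 454 in total.

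The stated 460 lies between these and is reproduced. This point does not change it.

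**3. Size of the bias in the primary comparison.** Assumptions, because the article gives only one overall dropout figure: the same true abstinence in both arms, 20% or 35% (the plan's two rates); attendance as listed; attendance independent of abstinence; 230 per arm.

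- Observed rate = true rate × proportion attending.
- With d = p2 − p1, p̄ = (p1 + p2)/2, SE0 = √(2p̄(1 − p̄)/230) and SE1 = √((p1(1 − p1) + p2(1 − p2))/230), the false-positive probability is Φ((d − 1.96 SE0)/SE1) + Φ((−d − 1.96 SE0)/SE1).

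Worked case, 20% true abstinence with attendance 70% (QT) and 90% (WQ): p1 = 0.14, p2 = 0.18, d = 0.04, SE0 = 0.0342, SE1 = 0.0341, giving 0.2144 + 0.0009 = 0.215.

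| True abstinence | Attendance QT / WQ | Observed QT / WQ | Odds ratio | P(two-sided P < 0.05) |
|---|---|---|---|---|
| 20% | 80 / 80 | 16% / 16% | 1.00 | 5.0% |
| 20% | 75 / 85 | 15% / 17% | 1.16 | 9.0% |
| 20% | 70 / 90 | 14% / 18% | 1.35 | 21.5% |
| 35% | 75 / 85 | 26.25% / 29.75% | 1.19 | 13.3% |
| 35% | 70 / 90 | 24.5% / 31.5% | 1.42 | 38.6% |

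Reversing the gap gives the mirror image in favour of QT. It can also hide a real effect: with true rates of 20% and 35%, the power to find WQ superior is 87.7% at 80/80 (16% v 28%), 67% at 85/75 (17% v 26.25%) and 40% at 90/70 (18% v 24.5%).

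**4. Sensitivity to independence.** Suppose abstinence among non-attenders is half the overall rate. Observed rate = true rate − (proportion not attending) × (true rate / 2). At 70/90 this gives 17% v 19% (true 20%) and 29.75% v 33.25% (true 35%), with false positives of 8.6% and 12.7%. If no non-attender is abstinent, nothing is subtracted and the rate is 5% at any gap.

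**5. What the overwritten outcome would have shown.** Suppose the gap comes only from CO refusal, self-reports are accurate, true abstinence is 20% and uptake is 70/90. The primary shows 14% v 18%. Self-reported PPA as defined shows 20% v 20% and points to uptake. Under the rule as worded it also shows 14% v 18%.

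**The case against.** The strongest reply is that the literal reading is strained. Refusing a validation test most naturally bears on the validated outcome, and for that outcome the rule only restates the definition, since an unconfirmed participant is not a success. The self-reports are still collected, and the later visits have no test to refuse. On this view the sentence is loosely drafted, not a decision to overwrite. That is fair as to intent, but the rule as written is unrestricted and gives a result that contradicts the outcome definition.

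A reader might also infer more than the article supports:

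- *That any difference in attendance creates a false effect.* It does not. Some of those unobserved must be abstinent; dropout confined to continuing smokers adds no bias. Equal attendance with equal true abstinence creates no false difference.
- *That attendance will differ, or will favour WQ.* Nothing shows this. QT counselors make repeated call attempts and may contact relatives and friends; WQ users receive reminders. The follow-up procedures and the 100 RMB payment are described without distinction by arm, and the Discussion says telephone follow-up staff are blinded.
- *That self-report is the plan's only check, or a complete one.* It can reveal CO refusal only. People lost to follow-up have no self-report, so bias from that source stays hidden after the fix as well.
- *That the absence of a sensitivity analysis is an error.* A journal article commonly leaves this to a fuller document that is not shown.

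**Conclusion.** The point holds as a defect in a stated rule. Its firmest part needs no assumption: as worded, the refusal clause contradicts the definition of 1-month self-reported PPA and makes that outcome nearly a copy of the primary.

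The bias in the primary comparison is conditional. It needs abstainers among those not tested and a between-arm difference in how many there are. The ranges of about 9% to 13% (10-point gap) and 22% to 39% (20-point gap) rest on assumed gaps and on attendance being independent of abstinence; they fall towards 5% as abstinence among non-attenders falls to zero. They show why the self-reported comparison is worth protecting. They do not predict what this trial will find, and they are no reason to abandon missing-as-smoking for the primary outcome.

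**What to change.** 1. Keep missing-as-smoking for the primary outcome.
2. Add a sentence to the Statistical analysis plan section: the CO-refusal clause applies only to the biochemically validated 1-month outcome; self-reported PPA uses the self-report as given, with only those lost to follow-up at that visit counted as smokers.
3. Report by arm, among 1-month self-reported abstainers, how many took the CO test.

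A sensitivity analysis for loss to follow-up, such as a range of assumed smoking odds among the missing, would be a useful option but is not needed to correct this point.

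The cost is a sentence of wording and one table from data already planned for collection. Sample size and trial conduct do not change. It should be settled before the data are analyzed, so that the scoring of 1-month self-reported PPA is not chosen after the results are known.

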### Interventions

#### Quitline-based treatment (QT group)

Participants in the QT group will receive standard proactive quitline services from China Professional Quitline ([name]) for 4 weeks using a multi-call quitline protocol [19]. The first session will focus on quitting history, motivation, self-efficacy, social support, and planning in advance of the quitting date. Smokers will be reminded in the second session to quit smoking completely from the quitting date, be provided with the practical information on how to quit. The sessions followed the quitting date (up to three sessions) will focus on building cessation skills and relapse prevention. Three Chinese-speaking counselors will provide the quitline services. All of them possess at least a bachelor’s degree in medicine or nursing, and have received more than 60 h of training in smoking cessation counseling.

To improve the participants’ adherence of the quitline intervention protocol, the counselors will call them at three time points for three consecutive days during each session, arrange the next session time for the participants, and contact the participants’ relatives and friends whenever necessary.

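### The set labelled ITT drops randomised participants who do not use services, so the primary comparison is not between the groups as randomised and may be biased in either direction

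*Protocol article*

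**What the plan says.** The Statistical analysis plan section of the protocol article first sets a missing-outcome rule: "By intent-to-treat analysis (ITT), participants who are lost to follow-up or refuse to participate in the validation tests will be considered as continuing smokers". The next sentence sets the analysis population: "Participants who do not use smoking cessation services after randomization will be excluded from the ITT analysis data set".

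The same section adds a per-protocol analysis of the primary outcome. It requires at least one telephone session in QT; in WQ it requires 20 or more days of mini-program use plus more than 10 group messages. Study design and Randomization and allocation describe a 1:1 open-label trial, and Sample size sets 230 participants per arm.

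Service use arises differently in each arm:
- **QT:** the service is delivered by outbound calls. To support adherence, "the counselors will call them at three time points for three consecutive days during each session", and relatives or friends may be contacted (Quitline-based treatment).
- **WQ:** participants are sent a QR code and must open the mini program or take part in the group. Daily messages and reminders are sent, and low users are telephoned (WQ modality-based treatment).

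The article does not say what counts as use for the exclusion and gives no expected share of non-users in either arm.

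**The concern.** Randomisation makes the two groups comparable only as allocated. Removing people for something they did or did not do after allocation breaks that, and more so when participants know their arm and the behaviour means something different in each. In QT a user is someone who answers a call; in WQ it is someone who opens a program or joins a chat. The people removed from one arm need not match those removed from the other in number or in prognosis.

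The two adjacent rules also disagree. A participant who never engages and is then lost to follow-up is a treatment failure under the first and leaves the denominator under the second.

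No other described analysis repairs this, because the per-protocol set also selects on use. At stake are the primary effect estimate, the secondary abstinence comparisons made on the same set, and the nominal 5% error rate.

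**Working it through.** **1. The plan's own figure.** Inputs from Sample size: "significance level of 0.05 for a two-sided test"; 90% power; QT abstinence "conservatively estimated as 20"%; "an increase in abstinence rate of 15% in the WQ group compared with the QT group", read as 20% vs 35%; 20% dropout.

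n = [1.960·√(2·0.275·0.725) + 1.282·√(0.20·0.80 + 0.35·0.65)]² / 0.15² = 184.1, or 185 rounded up. Then 185/0.8 = 232 per arm, and 184/0.8 = 230. The stated 230 per arm is reproduced to within rounding and is not in dispute.

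**2. Model for the exclusion.** Let p be abstinence among all randomised in an arm, u the share of non-users and r abstinence among non-users. The rate in the analysed set is

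p* = (p − u·r)/(1 − u), with n* = 230·(1 − u).

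The rejection probability is that of a two-sided pooled two-proportion normal test:

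Φ[(d − 1.96·se₀)/se₁] + Φ[(−d − 1.96·se₀)/se₁],

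where d is the difference in p*, se₀ the pooled and se₁ the unpooled standard error. The values of u and r are assumptions, since the article gives neither.

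**3. No true effect (p = 20% in both arms, r = 5%).**

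Worked case, QT 5% / WQ 20% non-use:
- QT: (0.20 − 0.05·0.05)/0.95 = 20.8%, n* = 218.5
- WQ: (0.20 − 0.20·0.05)/0.80 = 23.75%, n* = 184
- d = +3.0 points

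| Non-use QT / WQ | Difference, WQ − QT | Rejects for WQ | Rejects for QT | Two-sided total |
|---|---|---|---|---|
| 10% / 10% | 0.0 points | 2.5% | 2.5% | 5.0% |
| 5% / 10% | +0.9 points | 4.1% | 1.5% | 5.6% |
| 5% / 20% | +3.0 points | 10.7% | 0.4% | 11.1% |
| 20% / 5% | −3.0 points | 0.4% | 10.7% | 11.1% |

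Equal non-use of 5% or 20% also gives 0 points and 5.0%. A more extreme QT 5% / WQ 30% gives 26.4% vs 20.8% and 25.3% rejection; by symmetry the reverse shares give the same total with the sign changed.

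Sensitivity to r at QT 5% / WQ 20%: +3.9 points if no non-user quits (r = 0), and +2.0 points if r = 10%.

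**4. True effect as planned (20% vs 35%, r = 0).**
- All 460 kept: +15.0 points, power 95.2% at 230 per arm.
- Equal non-use of 10%: 0.20/0.90 = 22.2% vs 0.35/0.90 = 38.9%, +16.7 points.
- QT 5% / WQ 20%: 0.20/0.95 = 21.1% vs 0.35/0.80 = 43.75%, +22.7 points.
- QT 20% / WQ 5%: 0.20/0.80 = 25.0% vs 0.35/0.95 = 36.8%, +11.8 points, power 72.6%.

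**The case against.** A reader might infer that the rule favours WQ: the quitline pursues its participants by telephone while WQ users must act themselves, and the Discussion notes poor use of smartphone apps. The documents do not support that direction.
- The Background reports low utilisation of China's quitlines too, and a growing preference for chat over telephone.
- Eligibility requires skilled use of WeChat.
- WQ has its own outreach, including telephone reminders.
- A QT participant must still answer, and the per-protocol condition of at least one session implies that some may not.

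Three other strong readings also fail. First, low engagement is not removed from the result: only non-users are excluded, low users stay in, and the 20-day and 10-message thresholds belong to the per-protocol set. Second, the 5% error rate is not lost in every case: it holds under the null when exclusions match across arms in number and type. Third, non-users need not be nearly all smokers, because every participant is sent nicotine gum; a higher quit rate among non-users shrinks the bias.

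These points limit what can be said about direction and size. They do not rescue the rule. It is an explicit instruction rather than a detail left to a fuller plan, and nothing in the article ensures matched exclusions.

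**Conclusion.** The defect stands as an internal contradiction with a possible bias of unknown sign. The set named ITT is selected on an undefined, arm-dependent, post-randomisation behaviour; it conflicts with the missing-equals-smoking rule; and no abstinence comparison described retains all 460 participants.

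Under the illustrative assumptions, unequal non-use of 5% and 20% moves the estimate by about 3 points towards the arm with more non-users and roughly doubles the two-sided error to 11.1%. A 5% / 10% imbalance hardly matters (5.6%), and equal non-use with no true effect does no harm in this model. If WQ truly works as planned, no non-user quits and QT has the larger share of non-users (20% vs 5%), power is about 73% instead of 95%.

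Confidence is high on the contradiction. On direction and size the documents allow only a range. The point needs correction before analysis because it governs the primary outcome and the sponsor cannot know in advance which arm will lose more people.

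**What to change.** Delete the exclusion sentence. Analyse all randomised participants in their allocated arm for the primary and the secondary abstinence outcomes, and count missing or unvalidated outcomes as smoking under the rule already in place. Non-users who do provide an outcome keep that outcome.

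If a users-only set is wanted, keep it as a supplementary analysis under another name, such as modified ITT. Define use separately for QT and WQ before the data are examined, and report the number excluded by arm.

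The cost is one sentence and somewhat lower observed abstinence rates. No extra data are needed. With 230 per arm, power is 95.2% if 20% and 35% are the rates among all randomised. If the 20% dropout is counted as smoking on top of those rates (0.8·20% = 16% vs 0.8·35% = 28%), it is 87.7%, slightly under the planned 90%.
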